# Efficacy of repetitive transcranial magnetic stimulation combined with visual scanning treatment on cognitive and behavioral symptoms of left hemispatial neglect in right hemispheric stroke patients: study protocol for a randomized controlled trial

**DOI:** 10.1186/s13063-020-04943-6

**Published:** 2021-01-06

**Keywords:** Stroke rehabilitation methods, Transcranial magnetic stimulation, Brain pathology, Brain physiology, Functional laterality, Randomized controlled trial

## Abstract

**Background:**

Left hemispatial neglect (LHN) is a neuropsychological syndrome often associated with right hemispheric stroke. Patients with LHN have difficulties in attending, responding, and consciously representing the right side of space. Various rehabilitation protocols have been proposed to reduce clinical symptoms related to LHN, using cognitive treatments, or on non-invasive brain stimulation. However, evidence of their benefit is still lacking; in particular, only a few studies focused on the efficacy of combining different approaches in the same patient.

**Methods:**

In the present study, we present the SMART ATLAS trial (**S**timolazione **MA**gnetica **R**ipetitiva **T**ranscranica nell’**AT**tenzione **LA**teralizzata dopo **S**troke), a multicenter, randomized, controlled trial with pre-test (baseline), post-test, and 12 weeks follow-up assessments based on a novel rehabilitation protocol based on the combination of brain stimulation and standard cognitive treatment. In particular, we will compare the efficacy of inhibitory repetitive-transcranial magnetic stimulation (r-TMS), applied over the left intact parietal cortex of LHN patients, followed by visual scanning treatment, in comparison with a placebo stimulation (SHAM control) followed by the same visual scanning treatment, on visuospatial symptoms and neurophysiological parameters of LHN in a population of stroke patients.

**Discussion:**

Our trial results may provide scientific evidence of a new, relatively low-cost rehabilitation protocol for the treatment of LHN.

**Trial registration:**

ClinicalTrials.gov NCT04080999. Registered on September 2019.

## Background

Left hemispatial neglect (LHN) is a disabling neuropsychological syndrome, which occurs in about 30% of persons with stroke [1]. LHN is a well-known predictor of poor long-term functional outcome [2], as it may be associated with more extended in-hospital stay, long term limitations in activities of daily living, and an increased risk of falling [3]. About 90% of persons with LHN have suffered a right hemispheric stroke [1]. Patients with LHN present deficits in perceiving, responding, consciously representing, and orienting attention toward the contralesional hemifield, usually the left hemifield [4, 5]. Consequently, this specific condition leads to a lack of awareness for objects, persons, and even for their own body parts in the left hemifield. Furthermore, LHN can be associated with a deficit in other clinical domains. Indeed, motor deficits involving the body’s contralateral side (i.e., left hemiplegia) are often present. This clinical picture can be aggravated by a lack of awareness for cognitive and motor deficits (i.e., anosognosia), particularly influencing rehabilitation and daily living activities [6]. Thus, the complexity of symptoms in LHN requires broad assessments and specific rehabilitation protocols.

Clinically, LHN is investigated with paper and pencil neuropsychological tests (e.g., lines bisection, letter, or star cancelation), which assess the ability to search for stimuli in space. Recently, however, neurophysiological diagnostic procedures were introduced for the functional evaluation of LHN. Specific paradigms indeed use visual evoked potentials (VEPs) [7, 8] to assess biases in the processing of lateralized (i.e., right or left) presented stimuli. These studies evidenced a correlation between visual-spatial attention deficits in LHN and a reduction in amplitude and later latencies of the N100 component for stimuli presented in the left neglected hemifield. N100 anomalies are observed both at the left and right parietal cortices and on frontoparietal areas. These results suggest that functional impairments in LHN involve both hemispheres and the cerebral network involved in spatial attention orientation [1, 9]. Indeed, influential theories sustained the idea that LHN is related to a dysfunction in the neural network subtending attentive spatial processing. In particular, several studies report an imbalance in interhemispheric activity due to hyperactivity of the left hemisphere in LHN patients [1, 10–12].

In the rehabilitation of LHN, it is possible to distinguish protocols based on cognitive treatments and non-invasive brain stimulation, such as repetitive transcranial magnetic stimulation (r-TMS) [13, 14]. Conventional cognitive treatments (CCT) of LHN involve different types of exercises aimed at reducing attentional bias for the ipsilesional space (e.g., prism adaptation) and promoting contralesional space awareness (e.g., visual scanning training) [15]. Although several studies demonstrated the efficacy of CCTs on improving short and medium-term LHN symptoms, the debate is still open about these treatments’ long-term efficacy [16]. Thus, over the past 20 years, the interest in rehabilitation approaches based on non-invasive brain stimulation has increased. In particular, transcranial magnetic stimulation (TMS) is a non-invasive method to modulate the cerebral cortex’s excitability. For instance, Brighina et al. (2003) [17] applied low-frequency (1 Hz) inhibitory repetitive TMS (r-TMS) in the healthy contralesional areas. The r-TMS treatment improved the clinical symptoms of LHN after ten treatment sessions. Improvements were stable even 15 days after treatment. This study provided encouraging initial evidence on the efficacy of interventions based on TMS. Indeed, several studies also investigated the combined and additive effects of various rehabilitation techniques on the same patient (i.e., TMS and CCT) [18–20] to potentiate the intervention.

However, methodological limitations emerged from these studies, such as reduced sample sizes, the lack of blindness of assessors, the lack of a general assessment of activities of daily living, and long-term follow-up. Thus, it is still necessary to understand whether the combination of different therapeutic approaches can have a clinically significant additive effect in reducing the severity of symptoms of LHN. Furthermore, combined protocols need to be studied in terms of their neurophysiological correlates to quantify better their effects over the interhemispheric imbalance and in terms of long-lasting clinical results.

This study’s central hypothesis is that, as observed in previous studies for right hemispheric strokes, clinical symptoms of LHN are correlated to an imbalance in interhemispheric activity due to hyperactivity of the left hemisphere [1, 10–12]. Inhibitory r-TMS on the intact left parietal cortex reduces the left hemisphere activation and can rebalance interhemispheric activity. Indeed, the most used TMS paradigms for the rehabilitation of LHN are based on the concept of interhemispheric rivalry [21, 22]. According to this model, the two hemispheres exert a reciprocal inhibition. In particular, the right and left parietal cortices are part of an interhemispheric and intrahemispheric frontal-parietal pathway that controls the orientation of attention in space [1]. Thus, the right parietal cortex’s damage causes disinhibition of the left parietal cortex and, therefore, a pathological over-activation of the latter. This left over-activation consequently inhibits the right contralateral hemisphere by increasing the healthy hemisphere’s inhibitory activity on the damaged hemisphere. TMS treatments, therefore, aims at rebalancing interhemispheric rivalry by stimulating the parietal interhemispheric pathway, specifically inhibiting the areas of the left healthy parietal cortex [5, 23]. Thus, should r-TMS administered before a cognitive treatment, it might reduce the interhemispheric imbalance. Consequently, r-TMS may increase brain activity toward the left neglected hemifield and boost the effects of cognitive training. Specifically, in the present study, we hypothesize that a combined r-TMS and cognitive training protocol could be efficient in rehabilitating clinical and cognitive symptoms of LHN, reducing interhemispheric imbalance with a positive impact on activities of daily living.

### Aims and objectives

The aims of this study are: (1) to test the central hypothesis by assessing the immediate and long-term efficacy of a combined treatment based on r-TMS and visual scanning training (a conventional cognitive protocol based on the administration of a structured series of tasks aiming at improving spatial exploration abilities [13, 24] on the cognitive and behavioral manifestation of LHN in a population of patients with right-hemisphere stroke), (2) to assess the immediate and long-term efficacy of the proposed treatment on independence in activities of daily living, and (3) to investigate the clinical responsiveness of neurophysiological correlates and indexes based on visual evoked potentials (VEPs).

Our operational objectives and outcome measures are divided into primary and secondary outcomes to reach all these aims. The primary outcome is represented by (1) a specific assessment of visual-spatial attentive functions and behavioral symptoms of LHN with the Behavioral Inattention Test (BIT) [24]. The secondary endpoints consider the impact of the protocols on other clinical and neurophysiological indexes. In particular, we aim to test (2) the degree of functional independence with the Catherine Bergegò Scale, which considers the impact of LHN symptoms during activities of daily living (ADL) [25]. Furthermore, we test mobility with Motricity Index, Trunk Control Test, and Functional Independence Measure (FIM) [2, 26] that are measures of motor impairments, attentive functions with the Test of Attentional Performance (TAP), that is a computerized attention assessment. Finally, we tested (3) neurophysiological indexes of interhemispheric imbalance based on the latencies (IHTT, interhemispheric transmission time) and amplitudes (vABI, Visuospatial Attention Bias Index) of the N100 components of the VEPs.

## Methods

### Trial design and study design

We present the SMART ATLAS trial (**S**timolazione **MA**gnetica **R**ipetitiva **T**ranscranica nell’**AT**tenzione **LA**teralizzata dopo **S**troke; in English: repetitive transcranial magnetic stimulation in lateralized attention after stroke), a multicenter, randomized, controlled trial with pre-test (baseline), post-test, and 12 weeks follow-up assessments aiming at comparing the efficacy of inhibitory r-TMS, applied over the left intact parietal cortex of LHN patients, followed by visual scanning treatment (VS) [27], in comparison with a placebo stimulation (SHAM control) followed by the same visual scanning treatment, on visuospatial symptoms of LHN in a population of stroke patients. Our methodological approach provides two parallel groups (active r-TMS and SHAM placebo groups) with a 2:2 randomized allocation ratio in a superiority trial design. Figure 1 and Table 1 show the study flowchart and the study time points, respectively.

**Fig. 1 Fig1:**
[figure not shown]
Study flowchart. r-TMS, repetitive transcranial magnetic stimulation; VS, visual scanning

**Table 1 Tab1:** Study time points

Study period							
Stages ➔	Enrolment	Pre-allocation	Allocation	Post-allocation			Follow-up
**Weeks**	W0	W0	W0	W1	W2	W3	W15
**Time points**	T_0_			T_1_			T_2_
**Eligibility Screening**	X						
**Informed Consent**	X						
**Allocation**			X				
**Treatment**				X	X		
**Assessments**		X				X	X

### Participants

Patients with LHN due to stroke will be recruited in the Neurorehabilitation Unit of the IRCCS Istituto delle Scienze Neurologiche di Bologna (coordinating center) and the Villa Bellombra rehabilitation Hospital in Bologna (Italy). Subjects will be recruited accordingly to the following eligibility criteria:

Inclusion criteria:
Diagnosis of ischemic stroke of the right medial cerebral artery or right intracranial hemorrhagic stroke, confirmed by encephalic CT scan or MRI;Diagnosis of LHN with specific screening test (asymmetry score in the Bells test > 3);Inpatient or outpatient rehabilitation setting;Age between 18 and 80 years;Time after stroke between 3 weeks and 12 weeks; andAdequate language comprehension to give informed consent.

Exclusion criteria:
Medical instability at the time of enrollment, defined as the acute onset of an unexplained derangement of one or more vital parameters (temperature, blood pressure, pulse rate, respiratory rate, oxygen saturation, level of responsiveness) outside the normal range (e.g., fever, cardiac arrhythmias, respiratory insufficiency) and/or the onset of any new medical condition requiring unexpected additional diagnostic procedures and treatments (e.g., severe pain, reduction of urinary output);Presence of epileptogenic alterations of the EEG and/or previous epileptic seizures;Presence of intracranial implants of a metallic material;Presence of devices that could be altered by r-TMS, such as pacemakers, ventriculoperitoneal derivations, or baclofen infusion pumps;Absence of bone flap following decompressive craniectomy;Presence of alteration in the consciousness-vigilance rhythm;Cortical blindness and/or visual agnosia;Previous psychiatric disorders and/or history of substance abuse;Pregnancy state;Severe deafness not compensated by hearing devices;Severe reduction of visual acuity not compensated by optic lenses; andPrevious diagnosis of cognitive impairment.

Before enrollment in the study, the principal investigator (PI) will check the eligibility criteria. In particular, after verifying the eligibility criteria, the PI (or a delegate) will provide the potentially eligible person with all the information and details relative to the study in a simple language during an interview that will preferably take place in the presence of a caregiver.

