### Assignment of interventions

#### Allocation

The PI will generate a blocked randomization list (2,2 per group) using the online software QuickCalcs (www.graphpad.com). Only the PI will have access to the randomization list after its generation.

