Homogeneity vs. heterogeneity: For each outcome measure, the ANCOVA assumption of homogeneity of regression slopes will be verified [38]. In case the assumption is violated, a CHANGE measure (i.e., a score of gain in the specific outcome) will be considered in a 2 × 2 mixed-model ANOVA with the between factor group and the within factor time (posttest and follow-up).Normal distribution: Our primary outcome (the Behavioral Inattention Test) data will be analyzed after linear logistic transformation accordingly to the Rasch calibration, which ensures normal data distribution [39]. For the secondary outcomes, in the case normal distribution is not verified, a linear logistic transformation will be performed.In the case assumptions are verified, a mixed-model ANCOVA will be used with a 2 × 3 design, where the “between” factor will be the randomization group and the “within” factor will be the time of assessment, with the covariate pre-test baseline (T0) used to control for the LHN level before the beginning of the rehabilitation protocols.

In all cases, a two-tailed *t* test for independent samples will be employed to investigate the differences between groups. Data analysis will be performed using the MatLab (The Mathworks Inc.) and SPSS (version 13) softwares. We will accept a significance level of 5% (i.e., *p* value = .05) corrected for multiple comparisons when needed. Data from all randomized patients will be included in the analyses. Should data be missing at follow-up, data will be analyzed according to the intention to treat principle. However, participants will be contacted by telephone in the proximity of follow-up to ensure participant retention.

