## Conclusions

The SMART-ATLAS protocol implements a novel therapeutic approach for the rehabilitation of attentive spatial deficits in stroke patients by combining brain stimulation with cognitive treatments. The proposed approach is easily applicable and relatively low-cost.

Although a TMS stimulator is necessary for trial implementation, the visual scanning protocol is very flexible in terms of materials and tasks, and mainly paper and pencil material is required. Moreover, visual scanning can be implemented at the bedside, and also patients with severe motor impairments can easily carry out the tasks.

Although this is a multicenter trial, only two centers are involved. Thus, the generalizability of results may be limited. Further studies and replications of our protocol can improve results generalization. Should protocol efficacy be demonstrated, it could be implemented in ordinary clinical practice, thus providing an additional therapeutic option to reduce the burden of LHN and improve the clinical outcome of patients with right hemispheric stroke.

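### The ANCOVA adjusts only for the T0 score although entry spans 3 to 12 weeks after stroke; pre-specifying time since stroke as a covariate would be a cheap gain in precision

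*Protocol article*

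**What the plan says.** Participants sets the entry window as "Time after stroke between 3 weeks and 12 weeks" and also accepts "Inpatient or outpatient rehabilitation setting". Conclusions notes that "Although this is a multicenter trial, only two centers are involved".

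Statistical analysis fixes the models:
- **Main model:** a mixed-model ANCOVA with group and time, "with the covariate pre-test baseline (T0) used to control for the LHN level before the beginning of the rehabilitation protocols". No other covariate is named.
- **Fallback**, if the regression slopes are not homogeneous: a gain score that "will be considered in a 2 × 2 mixed-model ANOVA with the between factor group and the within factor time (posttest and follow-up"). No covariate is named.
- **Group comparison:** an independent-samples t test, two-tailed, planned whichever model applies. No adjustment is described.

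Allocation describes a "blocked randomization list (2,2 per group"). It does not say whether one list serves both centres or each has its own.

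**The concern.** The T0 score measures how severe the neglect is at entry, not how far the patient is from the stroke. By Table 1, T1 is at week 3 and T2 at week 15 of the study. T1 therefore falls roughly 6 to 15 weeks after stroke (3 + 3 to 12 + 3) and T2 roughly 18 to 27 weeks after it (3 + 15 to 12 + 15). Two patients with the same T0 score may expect different spontaneous change over the same study interval. That is clinically plausible, but the documents do not quantify it.

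If time since stroke does predict outcome beyond T0, leaving it out has two effects. Explainable variation stays in the residual, and an arm that happens to enrol earlier patients has that difference carried into its estimate. With 28 patients per arm, such imbalance need not be small. Time since stroke must be established for every patient to apply the entry criterion, so no new data are needed.

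**Working it through.** **1. The plan's own figure.** Sample size gives 3.1 for variability, 2.84 for the effect, 10.5 for the squared sum of z values, and 25.2 as the result. Reading 3.1 as an SD and 2.84 as a difference, although the article labels them as squared quantities:

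N = 2 × 10.5 × 3.1² / 2.84² = 201.81 / 8.0656 = 25.02 per group.

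This is close to 25.2. Then 25 / 0.90 = 27.8, so 28 per group and 56 in total. No covariate adjustment enters this calculation. At 25 per arm the two-sided 5% power is 90.0%, against the stated 0.80, because 10.5 is the value for 90% power. That mismatch is a separate matter.

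**2. Validity of T0-only adjustment.** Simulation of 4,000 trials per setting, with 28 per arm, blocks of four, entry times uniform over 3 to 12 weeks and two equally likely centres. The joint partial R² of time and centre given T0 was assumed to be 0, 0.10, 0.20 or 0.30. Under no treatment effect, the T0-only model gave mean estimates between -0.002 and 0.018 and type I error between 4.5% and 5.3%. There is no bias and no inflation.

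**3. Chance imbalance in a single trial.** Assume uniform entry times, so SD = 9/√12 = 2.60 weeks. The arm difference in mean time since stroke has SE = 2.60 × √(2/28) = 0.69 weeks, giving a 95% range of ±1.36 weeks. With partial correlation r and SD 3.1, the resulting 95% shift in the estimate is 1.96 × 3.1 × r × √(2/28) = 1.62 × r:

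| Assumed r | Shift (points) | Share of 2.84 |
|---|---|---|
| 0.2 | ±0.32 | 11% |
| 0.3 | ±0.49 | 17% |
| 0.4 | ±0.65 | 23% |

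The contrast's own 95% half-width is 1.96 × 0.829 = 1.62 points. Each shift is a fraction r of that, so the usual interval already covers it.

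**4. Net precision gain.** Take 50 completers (56 × 0.90 = 50.4). Adding a covariate with partial correlation r multiplies residual variance by 1 - r². Estimating it has a price: for roughly normal covariates, expected contrast variance is proportional to 1/(N - 3 - p), with p covariates. Going from one covariate to two costs 46/45 = 1.022. Going from one to three costs 46/44 = 1.045. The equivalent number of patients is 50 divided by the net factor.

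| Assumed r | 1 - r² | Time alone: net factor | Equivalent n (gain) | Time plus uninformative centre: net factor | Equivalent n (gain) |
|---|---|---|---|---|---|
| 0.2 | 0.96 | 0.981 | 51.0 (about 1) | 1.004 | 49.8 (about 0) |
| 0.3 | 0.91 | 0.930 | 53.8 (about 4) | 0.951 | 52.6 (about 3) |
| 0.4 | 0.84 | 0.859 | 58.2 (about 8) | 0.878 | 56.9 (about 7) |

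**5. Downside.** In the simulation with both covariates unrelated to outcome, adding them lowered power from 92.1% to 91.0%.

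**The case against.** The strongest reply is that a T0-adjusted ANCOVA is a valid primary analysis and that further covariates are a matter of preference. The same argument could admit age, stroke type or care setting. The benefit rests on correlations that the documents do not give, and at r = 0.2 it is close to nothing. Both centres are in Bologna, the Blinding section standardises assessors through joint sessions and a manual, and both arms receive the same visual scanning programme, so a centre effect may be small. All of this stands. It limits the size of the point and is why centre is only optional. It does not remove the point for time since stroke: the article goes beyond leaving detail to a later plan and names the model and its covariate, and the variable is at hand for everyone.

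A reader might infer more, in three ways that the documents do not support:
- **That the contrast is biased.** Chance imbalance under randomisation is random error, and the standard error already allows for it.
- **That the trial is underpowered as a result.** The sample size assumes no gain from these covariates.
- **That allocation is unstratified and needs a separate list per centre.** The Allocation section is silent on this, a condensed article may omit such detail, and by Trial status ten patients were already randomised, so changing the scheme is not a trivial edit.

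**Conclusion.** The point holds as a modest, inexpensive improvement to a stated model, not as an error that threatens validity. The plan adjusts for T0 only in its main model and names no covariate in the fallback or the t test, despite a nine-week spread in time since stroke at entry. The consequence is forgone precision and an estimate more exposed to chance imbalance, and only if time since stroke predicts outcome given T0. For an assumed partial r of 0.2 to 0.4, the net gain from time since stroke is about 1 to 8 patients' worth of information among 50. The figures further rest on 10% loss, on 3.1 being an SD on the analysed scale, on uniform entry times for the imbalance range, and on the normal-covariate approximation for the net gain.

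**What to change.** Before the final analysis, and before any interim look at outcome by arm:
1. In the primary BIT model, pre-specify time since stroke at entry, in weeks and continuous, as a covariate alongside T0.
2. Carry the same covariate into the fallback gain-score model.
3. Take the between-group contrast from the adjusted model in place of the unadjusted t test.
4. Optionally add centre as a further covariate, decided now and not after results are seen.

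The cost is a few lines in the analysis section and one degree of freedom, or two with centre. If neither covariate is prognostic, about 1 point of power is lost. No new data are needed and the allocation procedure does not change.
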